#### Demographic and clinical information

Participants report their demographic (e.g., age, education, ethnicity) and clinical information (e.g., medical history, comorbidities, medications). Staff also extract patients’ medial history from their hospital chart. To explore how gender-related self-perceptions influence health outcomes and relational dynamics, participants complete the *Traditional Masculinity-Femininity (TMF) Scale,* a 6-item measure of self-ascribed masculinity and femininity. Psychometric properties have been established (Cronbach’s alpha = 0.94) (Kachel et al., 2016).

Relationship quality is assessed in 2 ways: (1) The primary outcome, participants’ perceived RQ, is evaluated using the *Dyadic adjustment scale (DAS)*, a 32-item questionnaire with well-established psychometric properties (e.g., Cronbach’s alpha = 0.96) (Spanier, 1976; Prouty et al., 2000; Spanier and Thompson, 1982). The DAS has been employed in research and clinical settings among various populations, including patients with heart disease (Spanier, 1976; Prouty et al., 2000; Spanier and Thompson, 1982). Scores range from 0 to 151, with higher scores indicating higher RQ. Scores ≥108 indicate high couple satisfaction; scores ≤70 indicate extreme couple distress (divorcing couples) (Spanier, 1976). The four subscales measure couple satisfaction, cohesion, consensus and affectionate expression (Spanier, 1976). (2) Couple dynamics are recorded during a 15-min conflict-resolution task, during which couples are instructed to discuss their top 3 topics that regularly cause disagreement in their relationship such as health, money, sex, or in-laws, with the intention of coming to a resolution. These recordings are then coded by 2 blinded independent reviewers (psychology staff and graduate students) using the *Brief Romantic Relationship Interaction Coding Scheme (BRRICS)* (Humbad et al., 2011), a standard procedural guideline for coding behaviors in romantic relationships. Routine spot checks are conducted by co-PI [name] (blinded) to ensure reliability among the coders. The BRRICS evaluates both individual and dyadic aspects of interactions between partners, including positive and negative affect, positive and negative reciprocity, demand-withdraw patterns, and overall relationship satisfaction (Wildey and Burt, 2018).

Other relationship-related variables include attachment style, sexual satisfaction, and relationship self-efficacy. Participants complete the *Experiences in Close Relationships Scale-12 (ECR-12)* (Lafontaine et al., 2015) assessing attachment orientations using the dimensions of attachment anxiety and attachment avoidance with two subscales of six items each (rating from strongly disagree = 1 to strongly agree = 7). Low scores on both subscales indicate higher levels of secure attachment (Lafontaine et al., 2015; Wei et al., 2007; Brennan et al., 1998). Validity and reliability (Cronbach’s alpha = 0.74–87) of the scale has been established (Lafontaine et al., 2015). The adapted version of the *Global Measure of Sexual Satisfaction (GMSEX),* a 6-item measure, was used to assess overall satisfaction with the sexual relationship. Each item is rated on a 7-point bipolar scale (e.g., good-bad, valuable-worthless), with total scores ranging from 6 to 42, where higher scores indicate greater satisfaction (Lawrance and Byers, 1998). The psychometric performance of the scale is strong (e.g., Cronbach’s alpha = 0.96) (Quinn-Nilas, 2023). The *Self-Efficacy in Romantic Relationships scale (SERR)* is a 12-item questionnaire measuring confidence in romantic relationships. Participants indicate on a 9-point scale (1 = do not agree at all; 9 = completely agree) how much they agree with statements such as “I am just one of those people who is not good at being a romantic relationship partner” or “I feel insecure about my ability to be a good romantic partner.” (Riggio et al., 2013) Scores are totaled in a positive direction (i.e., higher scores indicate higher self-efficacy in a romantic partnership). The measure has been deemed valid and reliable (e.g., Cronbach alphas >0.79) (Riggio et al., 2013).

#### Mental health

Participants symptoms of depression over the past week are measured with the 21-item *Beck Depression Inventory Second Edition (BDI-II)* (Beck et al., 1996). Total scores range from 0 to 63; <13 = minimal, 14–19 = mild, 20–28 = moderate, and ≥29 = severe. The BDI-II demonstrated strong high internal consistency (Cronbach’s alpha = 0.90–0.93) and test–retest reliability (García-Batista et al., 2018). The *Patient Health Questionnaire (PHQ-9)*, a 9-item, 4-point Likert scale (0 = not at all; 3 = nearly every day) assessing depressive symptoms over the past 2 weeks is also completed by participants. Scores range from 0 to 27; cut-off scores for moderate, moderately severe and severe depressive symptoms are 10, 15, and 20, respectively (Kroenke and Spitzer, 2002). The tool shows strong psychometric properties, including good internal consistency (Cronbach’s alpha = 0.89) and robust validity (Kroenke et al., 2001). Two measures of depression were used because they provide complementary information. The PHQ-9 coincides with DSM-IV criteria for major depressive disorder. The BDI-II is more detailed measure that assesses the severity of cognitive, behavioral, and physiological symptoms of depression. Participants’ generalized anxiety is evaluated with the *General Anxiety Disorder 7 item (GAD-7)* questionnaire, a 4-point Likert scale with a total score of 0–21, where 10–14 and 15–21 indicate moderate and severe anxiety, respectively (Spitzer et al., 2006). The GAD-7 demonstrated strong reliability, with a Cronbach’s alpha of 0.89 and a composite reliability index of 0.90. It also exhibited robust validity across procedural, criterion, construct, and factorial measures (Bolgeo et al., 2023). Patient participants’ cardiac specific anxiety was assessed with the 18-item *Cardiac Anxiety Questionnaire (CAQ).* The *CAQ* yields 3 subscales reflecting fear, heart-focused attention, and related avoidance. Patients rate, on a 5-point Likert scale (0 = never, 4 = always), how frequent a behavior occurs (e.g., “I avoid activities that make my heartbeat faster”). Responses are summed for a total score; scores >26 are considered elevated (Eifert et al., 2000). The CAQ has shown good internal consistency (Cronbach’s alpha = 0.083) and construct validity (Eifert et al., 2000; Leissner et al., 2022).

The *PTSD Checklist for DSM-5 (PCL-5)* is a 20-item questionnaire used to assess post-traumatic stress symptoms. Responses to trauma-related statements are rated on a 5-point scale (0 = not at all, 4 = extremely); scores ≥33 are indicative of probable PTSD diagnosis (Weathers et al., 2013). Participants are directed to focus on the cardiac event when responding. The PCL-5 demonstrates strong reliability and validity in assessing PTSD symptoms across diverse populations (Cronbach’s alpha>0.91) (Blevins et al., 2015). One partner-specific questionnaire, the 22-item *Zarit Burden Interview (ZBI),* assesses how partners feel when taking care of another person and indicates the degree of caregiver burden. Responses are indicated on a 5-point Likert scale (0 = never; 4 = nearly always). Total scores ≥17 are considered high burden (Al-Rawashdeh et al., 2016). Psychometric properties of the ZBI have been established (e.g., Cronbach alphas>0.80) (Bachner and O’Rourke, 2007). As noted, all the mental health scales have been validated and used with patients with cardiovascular disease (Al-Rawashdeh et al., 2016; Van Beek et al., 2012; Seng et al., 2010; Blanchard et al., 1996; Hammash et al., 2013; Moullec et al., 2015; Löwe et al., 2008).

#### Quality of life

General and disease-specific QoL is assessed with 3 questionnaires. All participants complete the *Rand 36-item Short Form Health Survey* (Ware et al., 1993) to assess QoL across eight domains: physical functioning, role limitations due to physical health, role limitations due to emotional problems, energy/fatigue, emotional well-being, social functioning, pain, and general health. The SF-36 is widely used and validated across various patient populations, including those with cardiovascular disease (Brazier et al., 1992; Ware and Gandek, 1998). Patients also complete the *Heart-related Quality of Life Scale (HeartQoL)* (Oldridge et al., 2014), a 14-item validated questionnaire designed to evaluate how heart disease impacts daily functioning. The HeartQoL includes a global health-related QoL score and separate physical and emotional subscales (Oldridge et al., 2014). Similarly, partners complete the *Quality of Life of Cardiac Spouses Questionnaire (QL-SP),* a validated 26-item measure with two subscales: emotional functioning (14 items) and physical and social functional dimensions (12 items) (Ebbesen et al., 1990). Psychometric properties have been established for all scales with Cronbach alphas exceeding 0.70 (Brazier et al., 1992; Oldridge et al., 2014; Thomson et al., 2013; Zangger et al., 2018).

#### Health behaviors

Smoking status is reported by participants and confirmed with CO concentration (<10 ppm) in an expired breath sample, using the Russell standard (West et al., 2005). Participants wear an *ActiGraph GT3X-BT accelerometer* on their non-dominant hand for 7 days to assess physical activity and sedentary behaviors. Self-reported frequency and duration of mild, moderate and vigorous physical activity is also measured using a modified and validated version of the *Godin Leisure Time Exercise Questionnaire (GLTEQ)* (Godin and Shephard, 1985). Two *adherence* measures are used: (1) Medication adherence is measured with 3-items (e.g., how often do you forget to take your medication?) and (2) CR adherence is calculated by the percentage of exercise sessions attended relative to those prescribed.

#### Physical/cardiovascular markers

Blood samples taken by a staff phlebotomist are analyzed for *total cholesterol (TC), high-density lipoprotein cholesterol (HDL-C), low-density lipoprotein cholesterol (LDL-C), triglycerides (TG), C-reactive protein (CRP), and hemoglobin A1C (A1C).* Saliva samples are collected using Salimetrics Oral Swab (Salimetrics, State College, PA) to assess *cortisol and inflammatory marker IL-6*. Following the Trier Social Stress Test Protocol (Birkett, 2011), 5 samples are taken: upon arrival, before and after the conflict resolution task and 20 and 40 min later. Samples are stored at −80°C and shipped frozen to Salimetrics for analysis. *Heart Rate* Var*iability (HRV)* is measured by continuous heart period recordings of R-R intervals sampled at the rate of 1,000 Hz using First Bodyguard 2 (Firstbeat Technologies, OyJyvaskyla, Finland) connected to 2 leads by pre-gelled (Ag/AgCl) disposable electrocardiograph electrodes attached beneath the right clavicle and left ribcage (Firstbeat Technologies, 2025). *BP* is measured with the BpTru using standardized procedures (Myers et al., 2008). Finally, weight, height and waist circumference are recorded.

#### HHT intervention participant evaluation

HHT group participants complete the *Group Climate Questionnaire (GCQ)* (MacKenzie, 1983), a 12-item instrument designed to assess group engagement, conflict and avoidance. Responses are recorded on a 7-point Likert scale, from 0 (not at all) to 7 (extremely). The treatment specific *HHT Satisfaction Survey*, a 22-item survey assessing participants’ experience and satisfaction with the HHT sessions and the online delivery of the intervention, is given to HHT participants after program completion.

#### HHT intervention attendance and fidelity

Participation in the HHT intervention is recorded by class *attendance* (% attended). To ensure that the HHT intervention is delivered as intended, two sessions of every 8-session group are randomly pre-selected, recorded and scored on study-specific *HHT intervention fidelity checklist* by two independent raters (psychology trainees). Points are given, and percentage calculated, for each key point that is outlined in the session-by-session HHT manual (Tulloch et al., 2017).

### Data monitoring

Adverse events are recorded and reported to the principal investigator for review. Endorsement of the suicide item of the PHQ-9 or BDI are reported immediately to one of the study psychologists for risk assessment and care. The Healing Hearts Together study was initially granted ethics approval without a Data Safety Monitoring Board (DSMB); it was not recommended nor inquired by ethics. Nonetheless, the PIs convened a DSMB committee in 2024, consisting of a psychiatrist, cardiologist and consulting statistician, to discuss data management for the study.

### Auditing

The study has undergone 2 routine internal audits: one divisional, investigator-initiated audit in February 2022 and an institutionally led audit in February 2023. No major infractions were noted.

### Statistical analyses

#### Sample-size calculation

An *a priori* calculation was performed using RQ as measured by the DAS at 8 weeks as the primary outcome. Sample size was derived in 3 steps. First, we examined the standard deviation (SD) of the DAS scores pre-post intervention (SDchange) of pilot patients and partners separately (i.e., HHT pilot data); all SDchange values were close to 10. The consensus of the study investigators and other clinical content experts was to identify a minimum clinically important difference (MCID) based on a small (0.20) to moderate (0.50) Cohen’s effect size. The difference between the HHT and UC groups in the mean change was 3.9 for a small to moderate effect size. This value is close to the commonly used minimum mean change score for the DAS (3.16) (Jacobson and Truax, 1991). Then, we used these values (SDchange = 10; MCID = 3.9) to calculate the sample size with PASS15 sample size software. With 210 couples assigned in a 1:1 fashion to the two groups, we will have 80% power to detect a difference of 3.9 in the change in the DAS between the HHT and UC groups (*α* = 0.05). Nonetheless, we aim to inflate our sample size to account for the design effect of clustering (design effect = 1 + (m-1)*ICC = 1.21 = 254 couples), assuming that our average group size (m) will be 8 couples and our ICC is 0.030. We further increased our sample size target to 304 couples to account for an expected 20% loss to follow-up. As such, we aim to recruit 304 couples but will have sufficient power to detect differences in the primary outcome with 210 couples.

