### Interventions

#### Healing hearts together intervention

Couples are invited to attend 8 weekly 2-h sessions facilitated by clinical psychologists with EFT training. Before providing the intervention, facilitators review information on CVD and its treatments, theory and practice of group interventions, and familiarize themselves with the HHT facilitator materials. An HHT facilitators manual was developed to standardize intervention delivery (Tulloch et al., 2017). Planned group size is 3–8 couples, with sessions available in the day or evening to accommodate participants’ work schedules. Since the onset of the COVID-19 pandemic (March 2020), however, groups have been conducted online using the secure platform Zoom; only one group was held in-person before the pandemic. During the program, participants are guided through seven conversations in which they learn to identify and improve communication patterns for positive interactions in relationships (Tulloch et al., 2021). EFT interventions allow couples to acknowledge their fears and vulnerabilities and solidify their sense of security and emotional connection by guiding partners to respond to these feelings in comforting ways (Johnson, 2004; Johnson, 2008). The intervention maintains principles from the *Hold Me Tight* program (Johnson, 2010) but, as alluded to above, centres on identifying the impact of CVD on relationship dynamics, including the recognition and processing of worries and emotions following a cardiac diagnosis or event, healing interactions, and discussing sexuality in a health context (Tulloch et al., 2021). Materials, such as in-class and take-home worksheets, didactic presentations, and videos, are incorporated to facilitate these conversations (Johnson, 2010; Tulloch et al., 2021). The session-by-session overview has been previously described (Tulloch et al., 2021). In brief, each session begins with a review of the previous session and its homework, followed by a didactic presentation, a video clip of a couple discussing EFT principles, a private dyadic conversation, a final group discussion, and a homework assignment. In addition, each couple receives a copy of the book, *Hold Me Tight*, in print or audio version (Johnson, 2008) to be read in-between sessions. Attendance is noted at each session. Participants are asked to inform research staff if they must miss a session, and if this is the case, they are sent presentation slides from the respective session for review. Participant feedback surveys are sent via email after each session. All sessions incorporate group discussions and private conversations between patients and partners. Group discussion allows couples to share experiences related to CVD with their partners and peers. Session two allows for participants to discuss their experiences as patients in a patient-only group and as partners of someone with CVD in a partner-only group discussion, both of which are guided by a facilitator. Zoom break-out rooms are used for dyadic-specific exercises; facilitators assist during these discussions. HHT intervention materials may be found here: https://iceeft.com/healing-hearts-together-relationship-education-program/.

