#### Planned statistical analyses

SPSS and HLM statistical software will be used to analyze the study data. Demographic and clinical variables reported by participants who complete assessments will be compared to those lost to follow-up to verify the representativeness of the cohort. Analyses will be with the intent to treat sample. Research staff record all cases of missing data, including non-retention of participants or withdrawal of consent. Where data are missing, the frequency and reasons for missing data will be recorded. Missing data will be statistically examined for patterns of systematic missingness, and an appropriate missing data strategy will be employed. In situations where data are missing, the data collected up to that point will be used, provided the participant has not withdrawn their consent or requested that the information be removed. For the *primary outcome*, a multilevel analysis of covariance with individuals’ DAS values at 8 weeks as the dependent variable and DAS baseline scores as the covariate at level 1 of the model. The study conditions (HHT vs. UC) to which couples were assigned will be dummy-coded and entered at level 2. To evaluate *secondary outcomes,* a three-level multi-level model for repeated measurements will be utilized. The analysis will include repeated measurements within individuals in Level 1, between-individual variability in Level 2, and couples in Level 3. Within-couple slope variances will be fixed at Level 2 but allowed to vary at Level 3 (Atkins, 2005). A linear parameter will model changes in outcomes from baseline to 8 weeks to 24 weeks. The study condition (HHT vs. UC) will be dummy-coded and modeled as a fixed effect at Level 3. Baseline patient control variables will be entered at Level 2. Binary outcomes will be modeled utilizing a logit link. Improved model fit between nested models will be evaluated using deviance statistics and a chi-square distribution. Effect sizes will be assessed with the pseudo-R squared statistic or Cohen’s d when appropriate. Full maximum likelihood estimation method will be applied for all analyses. For both primary and secondary analyses, we will also conduct stratified analyses for all outcomes by sex (male/female), CR participation (yes/no), and relationship quality (distressed/not distressed on the DAS).

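### The sample-size figures (210, 254, 304 couples) do not fit the planned design or each other: the clustering inputs are conservative, but the loss allowance is too small and the claim that 210 couples suffice contradicts the inflation

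*Protocol article*

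**What the plan says.** The section on sample-size calculation takes the SD of change from pilot data, "of pilot patients and partners separately (i.e., HHT pilot data); all SDchange values were close to 10", and then "we used these values (SDchange = 10; MCID = 3.9". The base result is "With 210 couples assigned in a 1:1 fashion to the two groups, we will have 80% power to detect a difference of 3.9", with α = 0.05.

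That base is multiplied by 1 + (m − 1) × ICC = 1.21 to reach 254 couples, "assuming that our average group size (m) will be 8 couples and our ICC is 0.030". The target then becomes 304 for an expected 20% loss to follow-up. The section ends by saying that the trial aims for 304 but "will have sufficient power to detect differences in the primary outcome with 210 couples".

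Three other parts of the article bear on this:
- The description of the HHT intervention: "Planned group size is 3–8 couples".
- The description of usual care: clinical follow-up, referral to cardiac rehabilitation and optional support groups. No HHT groups are run in this arm.
- The planned statistical analyses: a multilevel ANCOVA on individuals' scores, with "DAS values at 8 weeks as the dependent variable and DAS baseline scores as the covariate at level 1" and study condition at the couple level.

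**The concern.** There are three separate problems.

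(a) The inputs to the design effect do not describe the planned trial. With groups of 3 to 8, the average is 8 only if every group is full. The design effect is applied to all 210 couples, although only the HHT arm is treated in these groups. The calculation is a two-group comparison with one score per couple, while the primary model uses both partners.

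(b) The allowance for 20% loss appears to multiply by 1.2 rather than divide by 0.8.

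(c) The closing sentence returns to the figure that stood before clustering and loss were allowed for, and calls it sufficient.

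The trial began in October 2019, narrowed its eligibility in July 2023 and was still collecting data when the article was written. If recruitment falls short of 304, the 210 sentence is the one that would be used to justify stopping. A reader cannot tell from the section what power any given number of couples delivers.

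**Working it through.** **Inputs from the article.** Difference 3.9, SD of change 10, α = 0.05 (taken as two-sided, which reproduces the base figure), 1:1 allocation, ICC 0.030, m = 8, planned group size 3–8, loss 20%.

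**Assumed, not in the article.** Mean group size 5.5, the midpoint (3 + 8)/2. Within-couple correlation of change, rho, 0.3 to 0.7. Equal total variance in both arms.

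**Formula.** With n evaluable couples per arm, SE = 10 × √(v_HHT/n + v_UC/n). Power comes from the noncentral t distribution with 2n − 2 degrees of freedom and noncentrality 3.9/SE.
- One score per couple: v = 1 without clustering, or v = 1 + (m − 1) × 0.03 where the design effect applies.
- Both partners averaged, group variance added: v = (1 + rho)/2, plus (m − 1) × 0.03 where clustering applies.

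**Reproducing the plan.**
- v = 1 in both arms, 105 per arm: 80.3% power. The 210 is reproduced.
- 1 + 7 × 0.03 = 1.21, and 210 × 1.21 = 254.1. The 254 is reproduced.
- 254 × 1.2 = 304.8, which matches 304. Division gives 254/0.8 = 317.5, so 318.

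**(a) Design effect in the HHT arm only, one score per couple.**
- m = 8: 210 × (1.21 + 1)/2 = 232 evaluable couples; 232/0.8 = 290 recruited.
- m = 5.5: the design effect is 1 + 4.5 × 0.03 = 1.135; 210 × (1.135 + 1)/2 = 224 evaluable; 224/0.8 = 280 recruited.

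Both lie below 254 and 304. Counting both partners lowers the need further: 158, 180 or 200 evaluable couples at m = 8, and 152, 172 or 192 at m = 5.5, for rho = 0.3, 0.5 or 0.7.

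**(b) Loss allowance.** 304 × 0.8 = 243 evaluable couples, fewer than the plan's own 254. Power with one score per couple:
- 1.21 in both arms (the plan's inputs): 78.6%.
- HHT only: 82.1% (m = 8) or 83.4% (m = 5.5).
- For comparison, 318 recruited leaves 254 evaluable and gives 80.4% on the plan's inputs.

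**(c) The 210 claim.** The article does not say whether 210 means recruited or evaluable. If recruited, 20% loss leaves 210 × 0.8 = 168.

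| Scores used | Clustering | 210 evaluable | 210 recruited (168 evaluable) |
|---|---|---|---|
| One per couple | 1.21 in both arms | 72.5% | 62.7% |
| One per couple | HHT only, m = 8 | 76.3% | 66.7% |
| One per couple | HHT only, m = 5.5 | 77.7% | 68.2% |
| Both partners, rho 0.7 | both arms, m = 8 | 78.0% | 68.5% |
| Both partners, rho 0.7 | HHT only, m = 5.5 | 83.6% | 74.6% |
| Both partners, rho 0.3 | both arms, m = 8 | 85.8% | 77.3% |
| Both partners, rho 0.3 | HHT only, m = 5.5 | 91.3% | 84.3% |

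On one score per couple, the basis used to derive 210, no row reaches 80% once clustering is counted. With both partners, the answer depends on rho and on what 210 means.

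**The case against.** The best defence is that the clustering arithmetic is right and every input questioned under (a) errs on the safe side. Taking m at its maximum gives the largest design effect at the stated ICC. Inflating both arms over-covers usual care. Sizing on an individual SD gives the planned power for patients or partners alone before clustering, and is conservative for the joint model. An article may also leave the pilot within-couple correlation and a model-based power calculation to the full protocol or analysis plan. All of this stands. It confines (a) to inputs that do not describe the design and excludes any claim of a shortfall from those three choices.

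The defence can add that 210 may mean couples with outcome data, and that the two-partner model could deliver 80% at that number. This also stands as a possibility: at 210 evaluable couples, most of the two-partner range lies above 80%. But the article derives 210 from one score per couple without clustering, then inflates it for clustering, and gives no other basis for calling it sufficient.

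A reader might infer that 254 or 304 couples leave the trial underpowered because the design effect is wrong. The article does not support that: correcting those inputs lowers the requirement. A reader might also take the 80% as claimed for the inflated design; the article states it for 210 couples before clustering.

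**Conclusion.** The point holds in three limited parts. The clustering inputs contradict the described design, but conservatively: about 224–232 evaluable couples are needed on one score per couple, against 254. The loss allowance is 14 couples short on the plan's own terms (304 against 318), which gives 78.6% power on those terms and about 82–83% once clustering is confined to HHT. The statement that 210 couples suffice contradicts the inflation before it. On one score per couple, power is 72.5% to about 78% at 210 evaluable and about 63–68% at 210 recruited. With both partners it is about 78–91% and 69–84%, for rho from 0.7 to 0.3.

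The target of 304 is therefore adequate at the stated SD, difference and ICC. Allowing for the small number of HHT groups with Satterthwaite degrees of freedom, 243 evaluable couples still give 80.7% (m = 8, HHT only, one score). This rests on the ICC of 0.030: at 0.05 the same case needs 246 evaluable couples, and at 0.10 it needs 282. The two-partner figures rest on the assumed rho and on adding the group variance to the couple variance. They use change-score variance and credit no further gain from baseline adjustment.

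**What to change.** In the sample-size section:
- Replace m = 8 with the planned mean group size or the mean observed so far.
- Apply the design effect to the HHT arm only.
- Allow for loss by dividing by 0.8, and say so.
- Restate 254 and 304 with the power that each delivers.
- Delete the claim that 210 couples suffice. Alternatively, replace it with the power at 210 evaluable couples under the planned multilevel ANCOVA, using the within-couple correlation from the pilot patients and partners and stating its value.

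The cost is one recalculation from data that the team already holds and a few restated figures. No change to enrolment is needed.

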## Method

### Design

The study is a single-centre, RCT with parallel group design. After a baseline assessment, participants are randomized in a 1:1 fashion, using a computer-generated sequence utilizing permuted blocks of 4, 8 and 10 initiated by the institutional methods centre, to the HHT program or to UC. Since sex and participation in CR can have an impact on the study outcomes, randomization is stratified by patient sex (male/female) and participation in the University of Ottawa Heart Institute (UOHI) CR program (yes/no). The trial began in October 2019 and data collection is ongoing. The protocol was approved by our institutional research ethics board (OHSN-REB# 20190101-01H) and all participants provide informed consent. Figure 1 depicts the study design and cohort flow.

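### The target of 304 couples multiplies 254 by 1.20 instead of dividing by 0.80, so at 20% loss it leaves 243 couples, 11 short of the plan's own 254; the cost in power is small

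*Protocol article*

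**What the plan says.** All the figures are in the Sample-size calculation section of the Protocol article, which builds the target in three steps.

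- **Unclustered number.** From "SDchange = 10; MCID = 3.9", the section states: "With 210 couples assigned in a 1:1 fashion to the two groups, we will have 80% power to detect a difference of 3.9", followed by "in the change in the DAS between the HHT and UC groups (*α* = 0.05".
- **Clustering.** It inflates this with "design effect = 1 + (m-1)*ICC = 1.21 = 254 couples", "assuming that our average group size (m) will be 8 couples and our ICC is 0.030".
- **Attrition.** "We further increased our sample size target to 304 couples to account for an expected 20% loss to follow-up".

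The section ends by saying that 304 is the recruitment aim but that 210 couples would be enough for the primary outcome. It gives no power figure for 254 couples, or for 304 less the expected loss. Elsewhere, the intervention section says: "Planned group size is 3–8 couples".

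**The concern.** An attrition allowance is meant to leave the required number of couples once the stated fraction of those recruited has gone. The required number must therefore be divided by the retained fraction. Multiplying by one plus the loss rate always falls short, because the loss applies to the larger, recruited number.

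The recruitment target is the headline figure of the design, and the Design section describes data collection as ongoing, so the figure may still be in use. If it does not follow from the assumptions printed beside it, the number of evaluable couples at the planned loss rate is lower than a reader would take it to be.

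**Working it through.** **Inputs.** SD of change 10, difference 3.9, α = 0.05, power 80%, design effect from m = 8 and ICC = 0.030, and 20% loss all come from the Sample-size calculation section. 1:1 allocation also appears in the Design section. The sidedness of α is not stated. Two-sided is assumed because it reproduces 210; a one-sided test would need 164. The couple is taken as the unit with SD 10, as in the plan.

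**Step 1: the 210 reproduces.** The normal formula, n per arm = 2(1.96 + 0.842)² × (10/3.9)², gives 103.2, so 104 per arm. With the t distribution, power is 79.9% at 104 per arm and 80.3% at 105, so 105 per arm (210 couples) is the first to reach 80%.

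**Step 2: the 254 reproduces.** 1 + (8 − 1) × 0.030 = 1.21, and 210 × 1.21 = 254.1.

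**Step 3: the 304 reproduces only by the wrong operation.**
- Multiplying: 254 × 1.20 = 304.8, printed as 304.
- Dividing: 254 / (1 − 0.20) = 317.5, i.e. 318.
- Difference: 318 − 304 = 14 couples, or 4.6% of 304.

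**Step 4: what 304 yields.**
- At 20% loss: 304 × 0.80 = 243.2, i.e. 243 couples, which is 254 − 243 = 11 short.
- Loss that still leaves 254: 1 − 254/304 = 0.164, i.e. 16.4%.

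**Step 5: power after 20% loss** (t-based, difference 3.9, SD 10).

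| Situation | Design effect | Effective couples | Power |
|---|---|---|---|
| 254 analysed | 1.21, both arms | 254 / 1.21 = 209.9 | 80.3% |
| 304 recruited, 20% lost, m kept at 8 | 1.21, both arms | 243.2 / 1.21 = 201.0 | 78.6% |
| 304 recruited, 20% lost, m falls to 8 × 0.8 = 6.4 | 1 + 5.4 × 0.030 = 1.162, both arms | 243.2 / 1.162 = 209.3 | 80.2% |
| 243 analysed, average m = 5.5 (middle of 3–8) | 1 + 4.5 × 0.030 = 1.135, both arms | 243 / 1.135 = 214.1 | 81.1% |
| 243 analysed, clustering in the HHT arm only | 1.21, HHT arm | 121.5 / 1.21 = 100.4 (HHT), 121.5 (usual care) | 82.1% |
| 318 recruited, 20% lost | 1.21, both arms | 254.4 / 1.21 = 210.2 | 80.4% |

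The normal approximation gives 78.9% instead of 78.6% in the second row.

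**The case against.** A reader might infer that the trial does not deliver its 80% power. The case against that inference is strong, and most of it stands.

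- **Where the 80% is stated.** The section attaches 80% power to 210 couples, and 243 is more than 210. It never prints a power for the target after loss. This limits what can be called a broken promise, but it does not rescue 304. The 210 ignores clustering; with the plan's own design effect, 210 analysed couples are equivalent to 210 / 1.21 = 173.6, with power of about 72%. The evaluable number that the plan's reasoning calls for is 254.
- **The 78.6% depends on holding m at 8 after loss.** The plan does not say whether m = 8 is before or after attrition. If groups of 8 lose a fifth of their couples, power is 80.2%. This stands.
- **The design effect is conservative.** A mean of 8 is the top of the planned range of 3 to 8, and the Usual care section describes no HHT groups, so clustering of that kind arises in one arm only. Relaxing either assumption (m = 5.5, or clustering in the HHT arm only) puts 243 couples above 80%. This also stands, although the plan printed m = 8 and a single design effect for the whole sample, and the target should follow from what is printed.
- **The worst case is small.** A gap of 1.4 points from 80% is minor beside the uncertainty in an SD described only as close to 10 and an assumed ICC.

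None of this touches the step from 254 to 304. It is wrong for a 20% loss whatever the ICC, group size or power, and nothing elsewhere in the article corrects it.

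**Conclusion.** The recruitment target is wrong on the plan's own assumptions. It adds 20% where it should divide by 0.80, leaves 243 couples instead of 254 at the stated loss, and covers 16.4% loss, not 20%. The figure consistent with the plan is 318.

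The consequence for power is small: about 78.6% against 80.3% if the design effect of 1.21 is carried unchanged through attrition in both arms, and about 80% to 82% under the other readings of clustering shown above. The documents do not support the conclusion that the trial misses 80% power. These figures assume a two-sided test, the couple as the unit, SD 10, and no credit for the missing-data strategy, which the Planned statistical analyses section leaves open. The sentence should be corrected because the target is a figure that the trial relies on, not because the design is in danger.

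**What to change.** Change one sentence in the Sample-size calculation section, in one of two ways.

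1. State 318 couples as the number that leaves 254 evaluable at 20% loss. If recruitment follows the new figure, this costs 14 more couples.
2. Keep 304 and state that it leaves 243 evaluable couples at 20% loss, and 254 only if loss is at most 16.4%. Give the power as about 78.6% with the design effect of 1.21 in both arms, and say whether m = 8 is meant before or after loss. If the sponsor prefers to rely on smaller groups or on clustering in the HHT arm only, state that assumption and the power that goes with it.

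The second option needs no extra couples and no change to allocation, outcome or analysis. Its only cost is a slightly less favourable stated power or loss tolerance.
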